### Study interventions

#### Intervention procedures

Children receive the interventions in groups or “classes” of ~15-18 children, 1 hour and 30 minutes per week (three OC groups and three VA groups). The interventions will start in March 2024 (wave 1, one group per condition) and in September 2024 (wave 2, two groups per condition). About 50 children will participate in each experimental condition (OC, VA, CG), so 150 children in total. Accounting for an attrition of maximum 30%, final analyses would include a minimum of 35 children per group, ensuring adequate statistical power (see Statistical analysis plan and sample size calculation).

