#### A recent Orchestra in Class (OC) randomized controlled study

Our team recently performed an RCT that demonstrated for the first time that focused MIP in a group setting, as compared to traditional sensitization to music, can provoke robust cognitive and sensorimotor transfer effects [1]. Over the last two years of primary school (at start ~10 YOA), 69 children received musical instruction twice a week by professional musicians within the regular school curriculum. The intervention group learned to play string instruments through OC; the control group, peers in parallel classes, were sensitized to music via listening, theory, moderate practice on simple instruments, and some chorus singing (traditional mandatory Swiss music courses). Broad benefits manifested in the OC group as compared to the control group in terms of musical abilities, sensorimotor hand function and bimanual coordination (near transfer), but also of WM, attention, processing speed, cognitive flexibility, and matrix reasoning (far transfer). Learning to play a complex instrument in a dynamic group setting impacted development much stronger than classical sensitization to music, with the same duration and frequency.

This study on 10-12 years old children by our team is, to the best of our knowledge, the only RCT comparing OC training to sensitization to music, therefore distilling the added value of MIP as compared to more general music lessons, involving active listening, and some moderate practice. However, our study was a cluster RCT^1^; in the current study we propose a genuine RCT with stratified randomization (see Study design), that ensures a similar baseline in all groups.

Several other limitations manifested in our study [1]: 1) EF function was not extensively investigated (only one test per construct), 2) the children were already in advanced childhood, 3) no brain imaging was involved that may underpin and better explain the observed near and far transfer effects. Finally, using an active control group also learning music may have induced overlapping effects, and a passive control group lacked.

Open issues: Perform a genuine large-scale RCT comparing MIP to another art form and a control group in children at the start of their academic curriculum, with an optimal age for brain plasticity and learning, using a large EF psychometric battery and multimodal neuroimaging.

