## Statistics and methodology

### Statistical analysis plan and sample size calculation

The research statistician of the host institute of the principal investigator will assist with the behavioral analyses. Experts in MRI data analysis, machine learning, and multimodal data integration within the team will supervise both MRI data analysis and the combined multivariate analysis of behavioral and MRI data.

*Sample size*: We computed sample size separately for our main behavioral outcome (WM) and for fMRI and structural MRI data. Our sample size will consist of 50 children per group, and we account for an attrition of 30%, so for the final analyses, we will dispose of minimum 35 children per group.

For our main behavioral outcome WM: Based on our previous behavioral study on OC [1]: with an alpha=0.05 and power=0.80, the projected sample size needed to reach a similar effect size (GPower 3.1) *n*=48 is the total for a simple between-group comparison, thus *n*=24 per group.

For fMRI data: A cross-sectional study comparing visual working memory networks of two groups of 19 ADHD and 14 healthy children (8-12 YOA) using a similar design [104] obtained activation maps within groups and between groups with numerous clusters surviving to correction for multiple comparisons at *p*<0.05 FWE (family-wise error).

For structural MRI data: A study showed large developmental brain plasticity changes in gray/white matter volume and fractional anisotropy (FA) at the whole-brain level (*p*<0.05 corrected for multiple comparisons) using a longitudinal design in a group of 24 adolescents [105].

To address the issue of selective dropout, we adjusted our participant numbers to account for an anticipated attrition rate of 30%, while still meeting the necessary sample size criteria, computed above.

A longitudinal randomized controlled trial (RCT) with three measurement time points and sufficient sample sizes offers increased statistical power and helps mitigate the risk of false positive findings commonly associated with smaller, non-randomized studies.

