#### Planned statistical analyses

Step 1: we will study relationships between EF and brain data collected at baseline for all participants based on a priori hypotheses and also in an exploratory way, using repeated measures Analysis of Covariance (ANCOVA), general linear models (GLM), correlations, and regression analyses. Apart from verifying a priori hypotheses, an additional goal is to identify potential confounding factors affecting our main outcome: EF, and particularly WM performance. Those confounding factors include socio-economic status, extra-curricular activities, aerobic physical fitness, and sleep. Apart from studying the influence of these factors on the outcomes, they also allow nuisance factor control, which will allow to objectively evaluate the OC and VA impact on EF in the following steps.

Brain data will be pre-processed and analyzed using in-house script routines calling the last versions of the standard neuroimaging software pipelines (e.g. Statistical Parametric Mapping 12 (or later version if released; https://www.fil.ion.ucl.ac.uk/spm/). We will generate a population-specific brain template. Individual brains and activation maps will be normalized on this template, critical for the validity of longitudinal brain plasticity results [106].

Step 2: we will examine and compare the development in both experimental groups and the CG over time for the comprehensive set of EF and brain data separately (T0 vs. T1 vs. T2). We will use linear mixed models (LMMs) with the open source software R [107] to evaluate the longitudinal effects for all behavioral variables separately, comparing all three groups over two years. LMMs are flexible, powerful, statistical models that can consider several levels of clustering, continuous and qualitative explanatory variables, as well as unbalanced data (pertinent if attrition differs per group). For testing specific hypotheses, we will add specific brain data in those LMMs (f.i. WM associations with CEN functional connectivity).

Near transfer scores closely representing direct benefits from the art interventions on the trained domains (musicality: IMMA [86, 87], visuo-spatial aptitude: the cubes test [84], teacher’s judgements, ratings by independent judges; see Table 3) will be analyzed in the same way. The results allow evaluating individual learning and the effectiveness of the courses.

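### The 35-per-group power claim makes no allowance for teaching OC and VA in three classes each; the stated 24 is no longer met above a class ICC of about 0.043 (OC vs VA) or 0.086 (either vs CG)

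*Protocol article*

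**What the plan says.** Under Intervention procedures, the two art programmes run in classes of about 15-18 children, "1 hour and 30 minutes per week (three OC groups and three VA groups". Wave 1 has one class per condition and wave 2 has two. The same section says that at least 35 children per group will remain after 30% attrition and that this gives adequate power. Attrition / drop-outs repeats that 35 per group is needed for sufficient power.

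The calculation behind this is in Statistical analysis plan and sample size calculation. It takes its effect from the team's earlier OC study, "with an alpha=0.05 and power=0.80, the projected sample size needed to reach a similar effect size (GPower 3.1", and concludes that 48 "is the total for a simple between-group comparison, thus *n*=24 per group". No effect size, ICC, design effect or number of classes enters it.

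Step 2 of Planned statistical analyses proposes linear mixed models and says in general terms: "LMMs are flexible, powerful, statistical models that can consider several levels of clustering". It names no random effect, for class or for child.

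**The concern.** Individual randomisation balances the arms at baseline. It does not stop outcomes from becoming correlated afterwards among children who share a class for two years. The protocol itself gives reasons to expect some correlation: the Background credits interaction during ensemble playing with part of the earlier benefit, and the OC description lists imitation of the teacher and emulation among pupils as routes of learning. CG children attend outings about every six weeks and have no weekly class, so the arms differ in their clustering.

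Positive within-class correlation means that 35 children in three classes carry less information than 35 independent children. A power statement built on independence is then too favourable. If the analysis also left class out, standard errors would be too small. OC vs VA, where both arms are in classes, is most exposed, and it is the contrast that separates music from art teaching in general.

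**Working it through.** **Inputs from the protocol.** Required n is 24 per group at alpha 0.05 and power 0.80. There are about 50 per arm at the start, 30% attrition, and three classes in each of OC and VA.

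**Assumptions.** Two-sided test; equal class sizes; CG children un-nested; class ICC over 0 to 0.10.

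**The plan's own figures.** Attrition reproduces: 50 x 0.70 = 35. The 24 cannot be reproduced forward because the effect size is not stated. Solving backwards with the noncentral t, 24 per group at 80% power implies d = 0.826. At 35 independent children per arm, that d gives 92.6% power.

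**Design effect.** Children per class: m = 35/3 = 11.67. Design effect DE = 1 + (m - 1) x ICC = 1 + 10.67 x ICC.

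**Break-even ICC.**
- OC vs VA (both arms clustered): DE may reach 35/24 = 1.458, so ICC = 0.458/10.67 = 0.043.
- OC or VA vs CG (one arm clustered): the average of DE and 1 may reach 1.458, so DE = 1.917 and ICC = 0.917/10.67 = 0.086.

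These limits depend only on 35, 24 and three classes, not on d. They take no credit for baseline adjustment.

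**Power at d = 0.826 with 68 df.** The variance of the standardised difference is 2 x DE/35 for OC vs VA and (DE + 1)/35 for OC vs CG.

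| ICC | DE | Effective n, OC or VA arm | Power OC vs VA | Power OC vs CG |
|---|---|---|---|---|
| 0 | 1.00 | 35.0 | 93% | 93% |
| 0.02 | 1.21 | 28.8 | 87% | 90% |
| 0.05 | 1.53 | 22.8 | 79% | 86% |
| 0.10 | 2.07 | 16.9 | 66% | 79% |

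**Few classes.** Six classes in two arms leave 6 - 2 = 4 between-class df for OC vs VA. On 4 df, power is 73% at ICC 0, 66% at 0.02, 56% at 0.05 and 45% at 0.10. For OC vs CG with Satterthwaite df (about 6.4 at ICC 0.02), power is about 79% at ICC 0.02 and 70% at 0.05.

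**Interval width for OC vs VA.** Relative to independent children, the ratio is (2.776/1.995) x sqrt(DE): about 1.4 at ICC 0, 1.7 at 0.05 and 2.0 at 0.10.

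**Type I error if class were left out.** Two-sided error is 2 x [1 - Phi(1.96/sqrt(k))], with k = DE for OC vs VA and (DE + 1)/2 for OC vs CG. At ICC 0.02 / 0.05 / 0.10 this is about 7.5% / 11% / 17% for OC vs VA and 6% / 8% / 11% for OC vs CG.

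**The case against.** The best defence has three parts.

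**The ICC may be small.** The documents give none. Working memory is tested individually, and the shared exposure is 90 minutes a week outside school. At ICC 0.02 the effective n of 28.8 still exceeds 24. This stands: a reader might infer that the power is certainly not delivered, but the documents support only a conditional loss.

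**There is slack that the calculation does not count.** Thirty-five is a minimum. With no attrition (50 per arm, 16.7 per class) the OC vs VA limit is (50/24 - 1)/15.67 = 0.069. Baseline working memory is among the factors to be handled by covariates. An assumed baseline correlation of 0.5 would move the limit at 35 per arm to [35/(24 x 0.75) - 1]/10.67 = 0.089, before any df penalty. This also stands, but the plan's calculation claims neither credit.

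**Model detail belongs in the analysis plan.** Step 2 names no random effects, so it does not exclude class. A reader might infer that class will be ignored and the error rates inflated; the text does not say so, and the type I figures are only a warning. The objection does not reach the power claim, which the article states outright.

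Three further readings go too far:
- The 0.043 limit does not apply to every contrast. The primary hypothesis also compares with CG, where the limit is about twice as high.
- The protocol gives two teachers per class but does not say that teachers differ between classes, so separate teachers cannot be cited as a source of clustering.
- The contrast with the earlier cluster trial ("in the current study we propose a genuine RCT with stratified randomization") goes on to claim similar baselines. It does not claim that clustering is absent.

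**Conclusion.** The concern holds for the power statement. The claim that 35 per group is adequate is unsupported, because it rests on independent children while two of the three arms are taught in three classes each. By the design effect alone, the stated requirement of 24 fails above an ICC of about 0.043 for OC vs VA and about 0.086 for contrasts with CG.

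Those limits are not the whole story if class is tested on its own few degrees of freedom. OC vs VA then misses 80% power even at ICC 0, and OC vs CG falls just under it at ICC 0.02. The power percentages rest on the back-solved d of about 0.83 and on assumed ICCs.

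**What to change.** In Intervention procedures, Statistical analysis plan and sample size calculation, and Attrition / drop-outs, restate the power or the detectable difference separately for OC vs VA and for each arm vs CG. Allow for class delivery over an assumed ICC range, for example 0 to 0.10, and for the small number of classes. Any credit for baseline adjustment should be stated with the correlation assumed.

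In Step 2, state that the mixed model includes class as a clustering level for OC and VA, with CG children un-nested (or grouped by outing group if those groups are fixed), and a small-sample df correction chosen by the statistician.

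The work is a change of wording and a re-run of the power calculation, best done before outcome data are analysed. No extra children are needed. The downside is a less favourable stated power and clearly wider intervals: for OC vs VA on 4 df, about 1.4 times as wide at ICC 0 and 2.0 times at ICC 0.10.

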#### Description of interventions

##### Experimental intervention group 1: OC

Diverse musical styles will be applied to offer a varied and attractive program. Two teachers will instruct the class, one for the higher-pitched instruments (violin, viola) and one for the lower-pitched instruments (cello, double bass). First, based on mutual consent, the children choose their instrument (7 violins, 5 violas, 4 cellos, and 2 double basses for 18 children), composing a true string orchestra composed of four instruments with different pitch ranges. At the start, the child will play by bowing open strings smoothly (without using the left-hand fingers), and by plucking the strings with the right hand (pizzicato). Progressively, the fingers of the left hand will be used to stop the strings, first while playing pizzicato, and later in combination with more and more diversely articulated use of the bow (right hand). Meanwhile, the complexity of rhythms will increase gradually. After approximately one month, children take their instruments home and are encouraged to practice 20 minutes per day, five days per week in the 1^st^ year, and 30 minutes in the 2^nd^ year, verified via an online diary. Score reading is introduced in the 1^st^ year but fully applied in the 2^nd^. From the very beginning, the child will be made aware of being part of a polyphony. Learning will follow three paths: imitating the teacher, reading the score, and emulation among students. Small concerts will be organized to stimulate children and give purpose to their learning. The OC teachers are professional certified string players specifically prepared for the OC methods at the Accademia d’Archi, an accredited music school in Geneva specialized in string instrument education. They will be supervised and coached by the director of the Accademia d’Archi (SNSF scientific partner). Every three months, a video of the OC courses will be recorded. A short video of each individual child playing the same short piece will also be made. The videos allow rating the playing level and progress post hoc by independent professional string players.

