## Methods and design

### Study design

The proposed study is a 1) randomized (stratified), 2) three-arm, 3) open, 4) monocentric (primary schools in Geneva) 5) national (Switzerland) 6) intervention study.

Stratified randomization will be applied to compose equivalent groups, stratifying for the factors 1) age, 2) gender, and 3) socio-economic background to balance all groups for those factors.

3-arm design: one experimental group (OC), another art group (VA), and an active control group (CG). The study design is open, as the assigned group cannot be blinded. Blinding will only be applied at the randomization level and, when possible, during the statistical analyses.

However, participants in all groups will be ignorant of the more robust hypotheses for brain and behavioral plasticity for the OC and, to a lesser degree for the VA group. We will explain to the parents and their children that we will compare the potential impact on intellectual child development, following two distinct art interventions or cultural outings.

The psychometric battery consists exclusively of validated tests.

A full list of the psychometric battery tests and MRI measurements can be found in Tables 3 and 4 in section "Study procedures with timelines". Importantly, each EF construct is measured by multiple tests.

We will cope with test-retest effects by 1) using different versions, or different items, or different order of items of the tests at T0 (baseline, before the interventions), at T1 (after one year of interventions) and at T2 (after two years of interventions), and 2) by taking into account the test-retest effects in the CG between timepoints.

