##### Experimental intervention group 2: VA

Diverse forms of VA will be taught. There will be two certified art teachers per class, to ensure sufficient individual attention. The courses will center on four axes: collage, drawing, painting, and sculpting, to offer a varied and attractive program, but may include other activities from the visual arts. The four different activities take place in blocks of ~6-8 weeks. Like for the OC interventions, working on individual aspects such as line, shape, form, color and tone will be part of the interventions for each axis, but the goal is to produce holistic artworks. At the end of each axis, the final task consists of the autonomous creation of an original artwork by the child. After approximately one month, the children can take some materials home and are encouraged to do artwork for 20 minutes a day, five days per week in the 1^st^ year, and 30 minutes in the 2^nd^ year, verified via an online diary. Small exhibitions will be organized to stimulate children and give purpose to their learning. Every three months, a video of the VA courses will be recorded. A short video of each individual child working on or presenting their artwork will also be made. This, as well as photographs of the artworks, will allow independent art teachers to rate the children’s skill level and progress post hoc. The VA teachers are professional artists specifically prepared for the VA courses under the supervision of a specialist in child art education (SNSF scientific partner) of the HEP (Haute École Pédagogique) de Lausanne.

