Attention	Processing speed	"The Witch" (KiTAP)	Specific key for witch presented in window – respond as quickly and correctly as possible	[92]
	Selective and sustained attention	Ucancellation (child-friendly version of d2 test)	Respond to upright dog (tail left), upside-down monkey (tail right) - Ignore similar distractors	[94, 95]
Auditory selective attention	Speech in noise perception	International Matrix Test	Participants repeat 5-word sentences heard through headphones: first without, then with a white noise background (right ear – left ear – both ears)	[90]
Inhibition	Response inhibition (motor inhibition)	Go/NoGo – "The Bat" (KiTAP)	Specific key for bat only - Ignore cat	[92]
	Distractor inhibition (perceptual/cognitive inhibition)	Child-friendly Flanker Task	Left/Right arrow for center fish swimming direction - ignore surrounding fishes (congruent vs. in- congruent swimming direction), as quickly and correctly as possible	[96]
Cognitive control / flexibility (higher EF)	Perceptual switching (simple)	"The dragons' house" (KiTAP)	Match button press to dragon color as quickly and correctly as possible – 2 alternating colors	[92]
	Rule switching (complex)	Dimensional Change Card Sort (DCCS)	Sort cards based on changing rules (color, shape), separately and mixed, as quickly and correctly as possible	[97]
Reasoning (higher EF)	Abstract/logical	Matrix reasoning (WISC-V)	Inspect incomplete matrix – choose missing piece from 5 options	[89]
	Quantitative/analogical	Figure weight (WISC-V)	Inspect scale with missing weight – select balance option within time limit	[89]
Reasoning Daily life functioning	Executive functions	BRIEF questionnaire	Daily living assessment of children’s executive functions	[98, 99]
Learning and progress	N/A	Multi-media materials	1. Videos (orchestra) – rating on ≠ Likert scales by independent judges 2. Photos and videos (visual arts) – rating on ≠ Likert scales by independent judges	
Learning and progress	N/A	Teacher ratings (Likert scales)	Music: 1. pitch; 2. rhythm; 3. expression; 4. ensemble playing/singing; 5. motivation; 6. overall quality Visual Arts: 1. graphic skill; 2. color management; 3. expression; 4. originality; 5. motivation; 6. overall quality	
	N/A	Homework	Use an online app to track homework	
Others / Miscellaneous	N/A	Aerobic fitness	School gymnastic teachers report aerobic fitness on Likert scale	
	N/A	Demographic questionnaire	Questionnaire for parents (extensive, including extracurricular activities)	

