For the brain data we will use univariate and multivariate analysis methods. Individuals’ intensity of training, progress, demographic characteristics, physical aerobic fitness and appreciation of the courses will be considered.

Step 3: we will analyze all data in a multivariate data-driven thus exploratory way. Separately analyzing behavioral data and several kinds of brain imaging data, cross-sectionally and over time, provides extremely valuable information on these data. Additionally, combining diverse behavioral and multimodal brain MRI data within data-driven multivariate analyses may unravel hidden “covert” relationships [108, 109]. These advanced analyses will encompass two main axes. The 1^st^ axis will be concerned with group inferences, asking “what intervention-related changes can be observed on imaging data at the group level?”, while the 2^nd^ axis will be concerned with individual prediction: “Can imaging features predict behavioral outcomes at the individual level?” To this end, we will consider joint analyses of imaging data (structural connectivity, functional connectivity data considered together).

In the 1^st^ axis (group-level analysis), we will use two methods which have been used successfully on multimodal brain imaging data, each carrying different assumptions about linearity of relationships and distribution of variables: multimodal Independent Component Analysis (ICA) [108, 109] on the one hand, and Partial Least Squares (PLS) [110–112] on the other. We detail these methods below.

Joint, fusion, and linked ICA [113, 114] are variants of ICA that allow combining different types of data such as functional and structural neuroimaging data. These analyses could reveal joint changes in different imaging modalities (i.e. covariations in functional and structural connectivity measures) and allow to investigate differences between our three groups [108, 113].PLS is another powerful technique that can identify components of multivariate relationships between imaging and behavioral data [111, 115], notably PLS correlation models [111]. PLS and sparse PLS may reveal hidden relationships between battery tests and MRI measurements before and after the regimens (OC and VA) and show whether these relationships differ between the groups. Implementations of these approaches are publicly available in addition to several in-house extensions that allow using them in the most flexible way, including machine learning [74, 116].

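### Independent judges rate level and progress without planned masking to recording date, which can inflate the within-arm learning used to judge the courses

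*Protocol article*

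**What the plan says.** The description of the orchestra intervention (OC) provides for course videos every three months and adds: "A short video of each individual child playing the same short piece will also be made". On their use it says: "The videos allow rating the playing level and progress post hoc by independent professional string players". For visual arts (VA), videos and photographs of the artworks "will allow independent art teachers to rate the children’s skill level and progress post hoc". Table 3 lists the instrument for the orchestra arm as "Videos (orchestra) – rating on ≠ Likert scales by independent judges", with a matching entry for photos and videos in visual arts.

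On masking, the Study design section says: "Blinding will only be applied at the randomization level and, when possible, during the statistical analyses".

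Step 2 of the planned statistical analyses places the independent judges' ratings among the near-transfer scores. These are to be analyzed like the other behavioral variables, that is, by linear mixed models comparing the three groups over two years. It then says: "The results allow evaluating individual learning and the effectiveness of the courses". For the brain data, Step 2 says that individuals' "intensity of training, progress, demographic characteristics, physical aerobic fitness" and appreciation of the courses will be considered.

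**The concern.** A judge who knows that one clip was made near the end of a two-year course and another near its start will tend to expect the later one to be better. If that expectation enters the score, part of the recorded change belongs to the rater and not to the child. Using judges who are independent of the teaching removes a personal stake in the result, but it does not remove this expectation. Only hiding the time of recording does.

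At stake is the plan's evidence that the courses taught what they set out to teach. That evidence matters for interpreting the trial: a null result on executive functions reads differently if the children learned a great deal than if they learned little. An inflated learning score would blur that distinction in both art arms.

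**Working it through.** The article gives no figure for the ratings, so there is nothing to reproduce. The check sets the sections side by side and follows the consequence through.

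**1. What is rated, and under what masking.** Both intervention descriptions name two rated quantities, level and progress. The article does not say whether progress is a score in its own right or is derived from level scores. The blinding sentence uses the word only and names two stages, neither of which is rating. There are then two cases:
- Progress scored directly: the rater must know which item is later, so expectation can act.
- Level scored on dated items and progress derived: the rater still knows which item is later, so expectation can act on each level score.

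The exposure disappears only if level is scored with the time hidden. The article does not provide for that.

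**2. Effect on the change score.** Let G be a child's true gain from first to last recording and b the average shift due to expectation. Then

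expected observed change = G + b, and relative overstatement = b / G.

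This does not shrink as the sample grows.

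**3. Whether a comparison removes b.**
- The control group (CG) has cultural outings. It has no playing or coursework for these judges to rate, so there is no control-group change to subtract.
- Visual arts cannot stand in as comparator for the orchestra arm, because its judges, material and criteria differ. Its own b is unknown and need not be equal.
- The rhythm test (IMMA) and the cubes test, also in the near-transfer set, belong to the battery given to every child at each time point. They do have control-group data and are not affected.

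It also follows that the judges' ratings cannot enter a mixed model comparing three groups, although Step 2 assigns them to one.

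**4. Whether b carries into the brain analyses.** If every child's progress score rises by the same constant b, then for any brain measure X, Cov(X, G + b) = Cov(X, G). The variances are unchanged too, so correlations and slopes between children stay the same. A common shift alone does not bias those analyses.

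**5. Illustration of the mechanism only.** Assume no true change, an SD of change of 1, and 35 children in one arm (50 × 0.70 = 35, the article's minimum for final analysis). The chance that a two-sided 5% paired t-test finds improvement or decline is P(|T| > 2.032), where T is noncentral t with 34 degrees of freedom and noncentrality b × √35:

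| Assumed b (SD of change) | b × √35 | Probability of significance |
|---|---|---|
| 0.10 | 0.59 | 0.09 |
| 0.25 | 1.48 | 0.30 |
| 0.50 | 2.96 | 0.82 |

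The nominal value is 0.05. Each b, and the absence of true change, is an assumption. The table shows that a modest shift is enough to matter to a one-arm test of change. It does not estimate the bias in this trial.

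**The case against.** The strongest reply is that the text does not fix a faulty procedure. Nowhere does it say that judges are told dates or order. Having each child play one set piece, rated after the fact, suits scoring level on shuffled clips and computing the difference. Treating the ratings as longitudinal outcomes in a mixed model fits that reading too. The blinding sentence follows a remark that the assigned group cannot be blinded, so it may concern arm allocation only. Clip order and item wording often sit in a rating manual, which a journal article would not reproduce.

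Much of this stands. A reader might infer that rating progress necessarily means the judges know the order. The article does not say so, and a masked procedure would be compatible with its wording. What remains is that the article makes a restrictive statement about where blinding applies, and that statement leaves the raters out. Arm allocation indeed cannot be hidden from someone watching a child play the cello, but the session can be.

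Two further inferences are tempting and are not supported:
- *That the courses could be declared effective with no skill gain at all.* Children with protocolled music or visual arts instruction in the preceding year are excluded, and orchestra pupils start with open strings. A true gain of zero after two years of lessons is not realistic. Two control-comparable tests also sit alongside the ratings.
- *That the brain analyses inherit the bias.* A shift common to all children leaves associations between children unchanged. The article also does not identify the progress variable there as the judges' score; teacher ratings appear under the same Table 3 heading.

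**Conclusion.** The point holds in a limited form. As written, the judges are not masked to time. Their ratings are used to evaluate the effectiveness of the courses, and no control-group rating exists to take out a shared expectation. The probable consequence is an overstated amount of learning within each art arm.

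The size of the overstatement cannot be derived from the documents. It depends on b relative to the true gain, and neither is given. The conclusion rests on two assumptions: that the blinding sentence means what it says about scope, and that judges who can see the timing are to some degree influenced by it.

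The working memory endpoint and the listed secondary endpoints are not built on these ratings, so the main trial conclusions are not threatened. This is a cheap improvement worth making before any judge sees dated material, because afterwards it can be recovered only by re-rating.

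**What to change.** - In both intervention descriptions, have the independent judges rate level only, after the last session. Present undated recordings and artwork photographs in random order across children and sessions.
- Where the item allows, use material that does not show the child's age: the sound track for pitch, rhythm and expression in the orchestra arm, and artwork photographs in visual arts.
- Compute progress as the difference between level scores.
- Add masking of the independent judges to session and date to the blinding statement in the Study design section.
- In Step 2, describe the judges' ratings as within-arm evidence of learning and remove them from the three-group mixed model. The rhythm test and the cubes test stay in it.

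The cost is wording and some file preparation, with the same judges and recordings. The protection is incomplete: items such as posture and bowing still need video, where the child's age remains partly visible even when clips are undated and shuffled.
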